# Prism adaptation combined with eye movement training for unilateral spatial neglect after stroke: Study protocol for a single-blind prospective, randomized controlled trial

**DOI:** 10.3389/fneur.2022.1081895

**Published:** 2023-01-05

**Keywords:** stroke, unilateral spatial neglect, prism adaptation, eye movement training, combined therapy

## Abstract

**Background:**

Unilateral spatial neglect (USN) is a complex neurological syndrome that often reduces rehabilitation outcomes, prolongs patients' hospital stays, and decreases their quality of life. However, the current therapies for USN have varying efficacy. We will explore a new treatment option that combines prism adaptation (PA) with eye movement training (EMT) for the treatment of USN after stroke.

**Methods:**

We will conduct a single-blind, prospective, randomized controlled trial to assess the efficacy of the combined intervention (PA & EMT) on USN in an inpatient rehabilitation setting. The study aims to recruit 88 patients with USN after an ischemic or hemorrhagic stroke. Participants will be randomly assigned to the following four groups: (1) PA group (*n* = 22), (2) EMT group (*n* = 22), (3) PA and EMT group (*n* = 22), and (4) control group (*n* = 22). All groups will receive 10 sessions of interventions over 2 weeks, 5 times per week. Blinded assessors will conduct a baseline assessment, a post-intervention assessment, and a follow-up assessment (2 weeks post-intervention). The primary outcome measure will use the Behavioral Inattention Test-Conventional Subset (BIT-C) and Catherine Bergego Scale (CBS) to assess the levels of USN. Secondary outcome measures will assess the patient's ability to perform activities of daily living using the Modified Barthel Index (MBI). Patients who completed all treatment and assessment sessions will be included in the final analysis.

**Discussion:**

This study will explore the effects of 10 sessions of combined interventions (PA & EMT) on USN and functional capacity. This study has the potential to identify a new, evidence-based treatment option and provide new ideas for the treatment of USN.

**Ethics and dissemination:**

The study protocol has been approved by the Nanchong Central Hospital. Written informed consent will be obtained from all the participants. The results of this study will be disseminated to the public through scientific conferences and a peer-reviewed journal.

**Trial registration:**

ChiCTR, ChiCTR2100049482. Registered on 2 August 2021, http://www.chictr.org.cn/showproj.aspx?proj=130823.

## 1. Introduction

Stroke is the second cause of death and the leading cause of disability worldwide (1). Poststroke patients usually suffer from multiple dysfunctions and complications that affect their health-related quality of life (2). Unilateral spatial neglect (USN) is a frequent and disabling condition after stroke, affecting approximately 30% of acute and subacute stroke survivors (3). USN is mainly related to damage to neural networks associated with spatial information processing and attentional control (4) and is defined as the inability to orient, detect, or respond to relevant stimuli in the visual field opposite to the brain lesion and unrelated to sensory and motor dysfunction (5). In clinical, approximately 40% of patients with USN are consistently affected by neglect symptoms (6). Compared to other stroke survivors, patients with USN are associated with poorer rehabilitation outcomes of other stroke symptoms (7) and longer hospital stays (8, 9). In addition, USN increases the consumption of health resources and adds to the burden on families (10, 11).

Since the early 1970s, various rehabilitation techniques have been proposed to reduce the disability caused by USN after stroke, including visual scanning training, trunk rotation, optokinetic stimulation, feedback or cueing, virtual reality, repetitive transcranial magnetic stimulation, and prism adaptation (PA) (12, 13). Monotherapy is frequently used in clinical research for USN, but overall, the level of evidence remains low. PA has been a hot research topic in recent years for the treatment of USN, with most studies supporting PA as an effective intervention while other studies were contradictory (14, 15). One possible explanation for the inconsistent results is that USN is a complex neurological syndrome with different manifestations for different neglect types and crossover symptoms between various neglect subtypes (16). Some researchers have suggested that combination therapy may produce more intense and long-lasting effects (17), and combination therapy is also the most frequently investigated USN intervention and shows promise for improving USN symptoms (18). The combination of different treatments may produce greater efficacy through similarities and differences in treatment mechanisms. Based on this, we speculate that combining PA with one approach will yield better results. In previous studies, Saevarsson et al. (19) and Choi et al. (20) combined PA with neck vibration and functional electrical stimulation, respectively, and both showed that the combined intervention better improved USN symptoms. However, the combination of these two studies only increased the number of interventions without mentioning the possible theoretical basis. Barrett et al. (21) inferred from animal models that stroke can induce classic visual–perceptual spatial neglect and motor intention deficits. Choosing a treatment option that intervenes in both areas may be a viable approach.

In this trial, we plan to combine PA and eye-tracking-based eye movement training (EMT) to treat poststroke USN. PA is a “bottom-up” approach (22), and it influences the level of sensory-motor through visuomotor adaptation to reduce symptoms of spatial neglect and, in particular, to improve spatial motor-intentional “aiming” deficits (23). PA was first proposed to treat patients with USN in 1998 (24), and a battery of studies has shown that PA improves not only the performance of patients with USN on neglect assessments (25–27) (e.g., BIT-C, CBS, and bell test) but also on neglect-related processes (15, 28–30). In addition, the sensorimotor after-effects of PA extend to the cognitive domain of patients with USN, for example, in complex spatial cognitive tasks required in daily life (navigation and terrain memory) (31), simple sound source localization abilities (32), etc. EMT is another USN treatment based on the attention disorder doctrine and belongs to the “top-down” approach. Similar to visual scanning training, EMT aims to improve the patient's ability to voluntarily orient his spatial attention toward the neglected side (33) and is characterized by repetitive practice of compensatory visual behaviors. Previous studies have shown that repetitive practice of compensatory visual behaviors can improve USN (34), and Leal Rato, M et al. also showed that eye gaze direction in patients with USN modulates spatial attention and that perception of direct gaze reduces visuospatial deficits in neglected patients (35). Although USN had been classically thought of as a “parietal syndrome” associated with lesions in visuospatial integration at the posterior parietal cortex (36), it has become evident that USN involves a disturbance in the widespread attention network (4), as well as the impact of attention deficits on visuospatial neglect, such as poor sustained attention and attentional shifting disorders (37). Therefore, EMT to improve visuospatial attention may be a treatment for USN, and this technique is still widely used in clinical practice (22).

Our study aims to investigate the efficacy of PA combined with EMT in the treatment of USN. We hypothesized that sequential use of these two interventions would produce a positive synergistic effect of 1 + 1 over 2, resulting in better improvement of USN symptoms in patients with poststroke.

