### 2.1. Study design

The study will be conducted as a single-blind, prospective, randomized controlled trial that will be conducted at the Second Clinical Medical College of North Sichuan Medical University. The protocol has been registered with the China Clinical Trial Registry (Item No.: ChiCTR2100049482). Our study will evaluate the effectiveness of EMT combined with PA in patients with poststroke USN, and the findings might provide a rationale for an approach of EMT combined with PA in patients with USN. A total of 72 patients will be recruited for this study and will be randomly assigned to four groups (1:1:1:1). All patients will receive conventional rehabilitation, as well as one of the three types of training: PA, EMT, PA, and EMT. To assess the efficacy, all participants will be assessed at three visits, including baseline, posttreatment, and 2 weeks after the end of treatment. The diagram and schedule for the study are shown in Figure 1 and Table 1.

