### 2.4. Sample size estimation

In the preexperiment, the changes in BIT-C scores before and after the intervention were 39.33 ± 18.717 for the combined intervention group, 26.33 ± 7.638 for the eye-movement training group, and 20 ± 2.828 for the PA training group. Using the PASS software, the probability α of occurrence of the Type I error was set to 0.05, the probability β of occurrence of the Type II error was calculated as 0.2, the calculation results showed that the combined intervention and eye-movement training groups required 20 samples each, and 9 samples were required for each of the combined intervention and PA training groups. Therefore, taking into account a 10% sample dropout rate, the total sample size was finally determined to be 88 cases, with 22 cases in each group.

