### 2.6. Interventions

All subjects will receive conventional rehabilitation during the intervention period, as well as appropriate interventions according to the group.

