### 2.12. Data analysis

IBM SPSS Statistics for Windows, Version 26.0 (IBM Corp., Armonk, NY, United States) will be used for statistical analysis. 2-tailed *P* < 0.05 will be considered a statistically significant difference. Continuous variables will be expressed as mean with standard deviation or median with interquartile range, whereas categorical data will be expressed as counts and percentages. Baseline comparisons will be used to examine potential differences between 4 groups. Age, time of onset, and MMSE will be analyzed by ANOVA or Kruskal-Wallis test. Sex, cause of damage will be measured using Chi-square tests. The Kolmogorov-Smirnov test will be used to evaluate the normality of distributions. If a normal distribution is confirmed, one-way ANOVA will be used to examine the effectiveness of intervention between the 4 groups at T1, T2, with Bonferroni correction for multiple comparisons as a *post hoc* test. Otherwise, Kruskal-Wallis (non-parametric test) will be used.

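### The Introduction hypothesises synergy, but the planned tests and the sample size address only whether the combination beats each single therapy

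*Protocol article*

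**What the plan says.** The hypothesis closes the Introduction of the protocol article: "sequential use of these two interventions would produce a positive synergistic effect". The same sentence glosses this as one plus one exceeding two. Read literally, that is a statement about the sum of two effects.

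The efficacy analysis is fixed in section 2.12: "one-way ANOVA will be used to examine the effectiveness of intervention between the 4 groups at T1, T2". Pairwise comparisons then follow, adjusted by Bonferroni. If normality is not confirmed, Kruskal-Wallis is used instead. The section names no interaction term and no contrast for additivity.

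Section 2.4 sizes the trial on "the changes in BIT-C scores before and after the intervention" in a pilot with three arms (combined, EMT, PA). It gives 20 per arm for combined against EMT and 9 per arm for combined against PA. The control arm does not enter the calculation.

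The abstract lists the arms as PA, EMT, both, and control. On background care, section 2.6 says: "All subjects will receive conventional rehabilitation during the intervention period, as well as appropriate interventions according to the group".

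**The concern.** Synergy and superiority over each component are different claims. If the two effects merely add, the combination still beats PA alone (by the effect of EMT) and beats EMT alone (by the effect of PA). A significant result on both pairwise comparisons is therefore what plain additivity predicts. None of the six pairwise comparisons among four arms equals the additivity contrast, and the global F test or Kruskal-Wallis test only asks whether the four groups differ.

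Training time is a second explanation for pairwise superiority. Sections 2.6.2 and 2.6.3 give 15-20 minutes per session for PA and 15 minutes for EMT. If the combined arm receives both as described, it gets 30-35 minutes of specific training against 15-20 or 15 in the single arms.

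At stake is the conclusion the trial can draw about its stated hypothesis. As planned, the analysis can neither support nor contradict it.

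**Working it through.** **1. The plan's own figures.** Inputs from section 2.4 (change in BIT-C, mean and SD): combined 39.33 (18.717), EMT 26.33 (7.638), PA 20 (2.828); alpha 0.05, power 0.80. Two-sided testing is from section 2.12. Method: two-sample t test, noncentral t, SD = sqrt((s1² + s2²)/2).

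- Combined vs EMT: difference 13.00, SD 14.29, gives 20 per arm.
- Combined vs PA: difference 19.33, SD 13.39, gives 9 per arm.
- 20 x 1.10 = 22 per arm; 4 x 22 = 88.

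Both sizes reproduce exactly, so the trial is sized for superiority over each single therapy.

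**2. The synergy contrast.** Assume the combined arm receives both trainings and control neither. Measured against control, synergy means

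(Combined - Control) > (PA - Control) + (EMT - Control),

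that is, I = Combined - PA - EMT + Control > 0. With the pilot means, I = 39.33 - 20 - 26.33 + Control = Control - 7.00.

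**3. Precision.** With 20 completers per arm, SE(I) = sqrt((18.717² + 7.638² + 2.828² + s²)/20), where s is the control SD. It is not given, so it is varied over the range of the pilot SDs. The effect detectable with 80% power is (1.96 + 0.84) x SE.

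| Assumed control SD | SE(I) | Detectable I | Control gain needed under pilot means (I + 7) |
|---|---|---|---|
| 2.828 | 4.61 | 12.9 | 19.9 |
| 7.638 | 4.87 | 13.7 | 20.7 |
| 18.717 | 6.19 | 17.3 | 24.3 |

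Under the pilot means, a detectable synergy would need a control gain of about 20 to 24 points, roughly equal to or above the PA arm's own 20.

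**4. Power for I over assumed control gains** (20 per arm, two-sided, normal approximation):

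| Assumed control gain | I | Power, control SD 2.828 to 18.717 |
|---|---|---|
| 5 | -2 | 7% to 6% |
| 7 | 0 | 5% (type I error) |
| 10 | +3 | 10% to 8% |
| 15 | +8 | 41% to 25% |
| 20 | +13 | 81% to 56% |

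**5. What the planned tests show when synergy is exactly zero.** Set the control gain to 7 and its SD to 7.638 (both assumptions), keep the pilot values elsewhere, and simulate 20,000 normal trials with 20 per arm. The one-way ANOVA is significant in about 100% of trials. With the pooled error term and six Bonferroni comparisons, the combination beats PA in 99%, EMT in 79%, and both in 79%. The test of I rejects in 5%. The 79% depends on pooling very unequal SDs: with a Welch test at 0.05/6, power for combined vs EMT is 52%. Either way, the plan would often find the combination better than both components with no synergy present.

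**The case against.** The best defence is that synergy is one loose sentence. The sentence before it gives the aim as the efficacy of the combination, section 2.1 speaks of its effectiveness, and the Discussion hypothesises a more positive and comprehensive effect and calls the study preliminary and exploratory. Sizing and analysis agree with that looser aim, and the pairwise comparisons do address it. This stands: the treatment comparisons remain valid, and rewording the hypothesis removes most of the mismatch. It does not remove all of it, because the Introduction's sentence is the explicit hypothesis and makes a quantitative claim that no planned test addresses. Nor is this a detail left to an unseen analysis plan, since the article states both the hypothesis and the efficacy test.

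Stronger readings are tempting, but the documents do not support them:

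- **That the pilot speaks against synergy, because 39.33 is below 26.33 + 20 = 46.33.** Adding raw gains counts background recovery twice in subacute patients who all receive rehabilitation. Any control gain above 7 makes the pilot means super-additive and any gain below 7 makes them sub-additive.
- **That pairwise superiority would be reported as synergy.** No section attaches such a claim or decision rule to any test.
- **That this is a declared 2x2 factorial with extra training time in the combined arm.** The article never calls the design factorial, section 2.6 does not describe the combined session or its length, and section 2.1 says all patients get one of three trainings although there are four groups. The layout and the training time are plausible inferences only.

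A fair limit on the remedy is that BIT-C is capped at 146 and one pathological subtest suffices for entry, so a ceiling could hide synergy on the additive scale.

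**Conclusion.** The concern holds as a mismatch between the stated hypothesis and what is tested and sized. Superiority over each component is tested; synergy is not. Adding the right contrast would not make the trial adequate for synergy: about 13 to 17 BIT-C points would be needed for 80% power. That range treats the three pilot SDs as known, assumes 20 completers per arm and a control SD between 2.8 and 18.7, and rests on the inferred 2x2 layout. A reader might conclude that the trial's design or its pairwise comparisons are invalid. They are not: sample size, allocation and data collection are untouched by this point. Severity: should-fix.

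**What to change.** - Restate the confirmatory hypothesis as superiority of the combination over PA alone and over EMT alone, which is what section 2.4 sizes.
- Prespecify the contrast Combined - PA - EMT + Control for change in BIT-C at T1, with CBS and T2 as supportive. Report the estimate with a 95% CI that is robust to unequal variances or bootstrapped, and report it even if the Kruskal-Wallis route is taken, since that test yields no such contrast. Label it exploratory and not powered, and note the possible ceiling on BIT-C.
- State that pairwise superiority alone will not be described as synergy.
- Say explicitly what the combined and control arms receive, reconciling sections 2.1 and 2.6, so that the reader can see whether the 2x2 reading holds and whether training time differs between arms.

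The cost is one extra contrast from the same four group means, some rewording and a more modest claim. No additional patients, visits or measurements are needed.

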## 2. Methods

This study was confirmed using a checklist in the SPIRIT reporting guidelines (38).

### 2.1. Study design

The study will be conducted as a single-blind, prospective, randomized controlled trial that will be conducted at the Second Clinical Medical College of North Sichuan Medical University. The protocol has been registered with the China Clinical Trial Registry (Item No.: ChiCTR2100049482). Our study will evaluate the effectiveness of EMT combined with PA in patients with poststroke USN, and the findings might provide a rationale for an approach of EMT combined with PA in patients with USN. A total of 72 patients will be recruited for this study and will be randomly assigned to four groups (1:1:1:1). All patients will receive conventional rehabilitation, as well as one of the three types of training: PA, EMT, PA, and EMT. To assess the efficacy, all participants will be assessed at three visits, including baseline, posttreatment, and 2 weeks after the end of treatment. The diagram and schedule for the study are shown in Figure 1 and Table 1.

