### 2.5. Randomization and blinding

A random number list is generated by a computer and consists of 88 random numbers. The random numbers were arranged from the smallest to the largest to obtain the serial number R. It is stipulated that group A (PA) with *R* = 1–22, group B (EMT) with *R* = 23–44, group C (PA & EMT) with *R* = 45–66, and group *D* (control) with R = 67–88. The resulting sequence of random assignments was placed in sequentially coded, sealed, impermeable envelopes. The investigator in charge of recruitment opens the envelope according to the order of patient enrollment and assigns the subjects to the appropriate subject group.

This study is a single-blind design, and only the investigator conducting the assessment is blinded to group assignment. The therapist cannot be blinded due to using the supervised intervention. In addition, blinding of subjects is not feasible due to the difference in intervention methods. All outcome assessments for this study will be conducted by a separate professional therapist who is not involved in any other part of the study. Moreover, participants will be unblinded when any clinical situation associated with adverse events or patient withdrawal occurs.

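### Section 2.1 recruits 72 patients where the abstract, sample size calculation and randomisation list all give 88, and its training sentence leaves no place for the control arm

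*Protocol article*

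**What the plan says.** Section 2.1 (Study design): "A total of 72 patients will be recruited for this study and will be randomly assigned to four groups (1:1:1:1"). Four equal groups out of 72 is 18 per group.

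Three other places give a different total:

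- Abstract, Methods: "The study aims to recruit 88 patients with USN after an ischemic or hemorrhagic stroke", followed by four groups of 22.
- Section 2.4 (Sample size estimation): "the total sample size was finally determined to be 88 cases, with 22 cases in each group".
- Section 2.5 (Randomization and blinding): "A random number list is generated by a computer and consists of 88 random numbers". The list is cut into four runs of 22, the last being group D, "control) with R = 67–88".

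On what the arms receive, section 2.1 continues: "All patients will receive conventional rehabilitation, as well as one of the three types of training: PA, EMT, PA, and EMT". Section 2.6 says: "All subjects will receive conventional rehabilitation during the intervention period, as well as appropriate interventions according to the group". Section 2.6.1 sets out the conventional rehabilitation, and Table 1 gives it its own row beside the three trainings. The abstract adds that every group has ten intervention sessions over two weeks.

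**The concern.** The recruitment total tells the trial when to stop, and the Trial status section says recruitment was still going on at publication. A study design section that is 16 patients short of the sample size section leaves two stopping points in one document, and the lower one does not deliver the planned power.

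The training sentence raises a second difficulty. Section 2.1 first names four groups and then gives every patient one of three trainings, so the fourth group has no place in it. Group D is the natural reference for each single therapy and for the hypothesis in the Introduction that the combination exceeds the sum of its parts. What it receives should read the same way throughout.

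**Working it through.** **1. Reproduce the plan's own figure.** Inputs from section 2.4 (change in BIT-C): combined 39.33, SD 18.717; EMT 26.33, SD 7.638; prism adaptation (PA) 20, SD 2.828; alpha 0.05; beta 0.2; dropout 10%. Two-sided testing is stated in section 2.12 and is assumed here for the sample size.

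The test is a two-sample t with SD = √((s₁² + s₂²)/2).

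- Combined vs EMT: difference 39.33 − 26.33 = 13.00; SD = √((18.717² + 7.638²)/2) = 14.29; d = 13.00/14.29 = 0.909. Smallest n per group with 80% power: 20 (power 0.800). Stated: 20.
- Combined vs PA: difference 19.33; SD 13.39. Smallest n: 9 (power 0.820). Stated: 9.
- Dropout: 20 × 1.10 = 22 per group; 4 × 22 = 88. Stated: 88.

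The 88 is reproduced.

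**2. Can 72 be given another meaning?**

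- Per arm: 72/4 = 18, below the 20 required before dropout.
- Evaluable total: 4 × 20 = 80, so 72 is not the number needed for analysis.
- Active arms only: 3 × 22 = 66, so it is not that count either.
- 80 × 0.9 = 72, but this would apply the dropout allowance in the wrong direction.

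None of these makes 72 a valid recruitment total.

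**3. Power for combined vs EMT** (pooled t, d = 0.909, two-sided alpha 0.05).

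| Total recruited | Per arm | Power, no dropout | Per arm after 10% dropout | Power after dropout |
|---|---|---|---|---|
| 88 | 22 | 0.838 | 19.8, taken as 20 | 0.800 |
| 72 | 18 | 0.755 | 16.2, taken as 16 | 0.702 |

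The Welch form gives 0.742 and 0.687 for the second row, and the normal approximation 0.779 and 0.730. For combined vs PA, power stays above 0.96 at 16 per arm under all three methods, so the loss falls on the EMT comparison.

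**4. Does 72 fit the randomisation list?** Section 2.5 describes one permutation of 88 numbers with no smaller blocks. Stopping after 72 leaves 88 − 72 = 16 allocations unused. The arms are equal only if those 16 contain exactly 4 from each group:

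C(22,4)⁴ / C(88,16) = 7315⁴ / C(88,16) = 2.863 × 10¹⁵ / 1.448 × 10¹⁷ = 0.020.

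About 2% of sequences would give 18:18:18:18. The median gap between the largest and smallest arm would be 4 patients.

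**5. The control arm, side by side.**

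| Place | What it implies for group D |
|---|---|
| 2.1, training sentence | One of PA, EMT, or PA and EMT |
| 2.5 | A separate control group of 22 |
| 2.6, 2.6.1, Table 1 | Conventional rehabilitation for all; no fourth training named |
| Abstract | Ten sessions of interventions, as for every group |

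The first row cannot stand with the second. The third suggests conventional rehabilitation without an added training. The fourth leaves that unclear.

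**The case against.** The strongest reply is that a careful reader can tell what is meant. Three places and a reproducible calculation fix 88, the allocation list itself has 88 entries, and nothing shows that anyone intends to stop at 72. That stands: the power loss is conditional on the lower figure being followed. It does not make the figure in 2.1 correct.

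Three stronger readings are tempting, and the document does not support them.

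- *Section 2.1 describes a different trial.* It does not. It keeps four groups, equal allocation, conventional rehabilitation for all and the three assessment visits.
- *The control arm's content is given nowhere.* Sections 2.6 and 2.6.1 and Table 1 point to conventional rehabilitation. The flowchart (Figure 1) is not shown in the text at hand, so its content cannot be counted as absent. What remains is a contradictory sentence in 2.1 and an unclear one in the abstract.
- *The 72 cuts power below 50% once Bonferroni is applied.* At alpha 0.05/6 = 0.00833, power is 48% at 18 per arm and 42% at 16. Section 2.12 does not state the number of comparisons, so six is an assumption. At the same alpha the planned 88 gives only 60% at 22 per arm and 54% at 20. Most of the shortfall from 80% therefore comes from the correction, which is a separate matter.

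The two parts of the consequence should also be kept apart. The power figures suppose exactly 18 per arm, whereas the list stopped at 72 would seldom produce that.

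**Conclusion.** The point holds. The total of 72 in section 2.1 is wrong as written, and the protocol's own calculation and list determine the right figure, 88. If 72 were used, power for combined vs EMT would fall from 84% to about 75% with no dropout, and from 80% to about 70% after dropout. These figures rest on the pre-experiment means and SDs, a two-sided alpha of 0.05 without multiplicity correction, and 10% dropout. The arithmetic in section 2.4 is not at fault; this is an inconsistency between sections. That 72 survives from an earlier plan is something a reader might infer, but the document does not say so.

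The training sentence in 2.1 contradicts both its own four groups and the control arm. The likely reading can be recovered from section 2.6 and Table 1, so this is a conflict to reconcile and not an undefined arm.

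**What to change.** In section 2.1, replace 72 by 88 (22 per group), to agree with the abstract and sections 2.4 and 2.5.

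Reconcile the training sentence in 2.1 and the abstract's sentence on ten sessions for all groups with sections 2.5, 2.6 and 2.6.1 and Table 1, so that one description of what group D receives applies throughout. Which description is correct is for the investigators to state.

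The cost is the rewording of two sentences in section 2.1 and one in the abstract. No allocation rule, endpoint or analysis changes.
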